### Study Intervention

#### Treatment of Trial Participants

The treatment process will include provision of implant-supported full-arch fixed prostheses (dental intervention, DE) and dietary intervention tailored to the dental status (dietary intervention consisting of nutrition education, DI). Subjects will be randomized to either a waiting period or treatment regarding dental intervention and dietary intervention. Ethical justification for the waiting period comes from the current waiting list in the regular care at the hospital. In order to improve the compliance with the protocol, all subjects participating in the study will have an alert in their patient record identifying them as participants to this protocol to alert administrative staff on the need to follow a stringent timing of follow-up appointments.

#### Dental Intervention

All participants will receive implant-supported full-arch fixed prostheses in at least one jaw (26, 27) and appropriate treatment in the opposing jaw regarding periodontal disease, caries, replacement of missing teeth and soft tissue disorders to get at least 10 pairs of occluding teeth (22).

Before surgery, a treatment plan will be made according to the clinical examination, study model and the CBCT data. Pre-surgery mock-up will be produced to guide implant placement and to facilitate the fabrication of the immediate prosthesis. A surgical guide with tooth set-up will be used for implant placement and bite registration, as needed.

After administrating local anesthesia any remaining tooth will be exacted atraumatically and the sockets will be carefully curetted. A crestal incision will be made and a full thickness mucoperiosteal flap will be reflected. For the preparation of the osteotomy site for implant placement, a modification of the drilling protocol according to the manufacture's recommendation will be followed as needed for immediate placement in case of the presence of residual teeth/roots. Tapping may not be used depending on the bone density to ensure primary stability of the implant. After the site preparation, 4–8 Nobel Active® implants (Nobel Biocare, Goteborg, Sweden) will be placed. Multi-Unit abutments (Nobel Biocare, Goteborg, Sweden) will be placed onto the implants. The abutment will be tightened with a torque of 35Ncm for straight multi-unit abutments and 15 Ncm for angulated multi-unit abutments. Healing caps will be placed on the abutments to support the peri-implant mucosa. The flap will be closed with a 5-0 resorbable suture (Vicryl, Johnson & Johnson Medical, Pomezia, Italy). Then, splinted impression will be taken at abutment level using an individual open tray. Pre-surgery mock-up or surgery guide with tooth set-up will be used to register the occlusal relationship. Patients will receive amoxicillin (Xinya Co, 500 mg, 3 times/day for 7 days). Decongesting nasal drops (phenylephedrin, 0.1 ml, 3 times/day for 3 days) will be prescribed if sinus elevation will be performed. Mouth rinsing with chlorhexidine 0.12% three times per day and modified oral hygiene procedures will be prescribed for the first 2 weeks of healing (sutures still in place).

A screw-retained, metal-reinforced, acrylic resin interim restoration will be delivered within 24 h of surgery. All centric and lateral contacts will be assessed and modified, until occlusal contacts are uniformly distributed on the entire prosthetic arch. Sutures will be removed at 2 weeks. After a healing period of 4 month, a definitive screw-retained, full-arch prosthesis will be delivered.

#### Brief Nutrition Education

The nutrition education will be conducted based on the health Belief Model (HBM) (28) addressing perceived susceptibility and severity of lacking the targeted behavior, perceived benefits and barriers of carrying out the targeted behavior, cues to action, and self-efficacy. With behavioral goals being increasing an individual's likelihood of food intake regarding fresh vegetables, fresh fruits, and high-quality protein foods (i.e., poultry, meat and aquatic product), the nutrition education session has been designed to be culturally tailored.

Participants will receive a 20-min coordinated nutrition education in the form of a slideshow presentation by a nutritionist in the clinical setting. On completion they will receive a copy of a pamphlet prepared in three parts (overall dietary goal, recipe examples mainly composed of softer and easy-to-chew food, and recipe examples composed of various food without restriction on the texture). The advice has been compiled with reference to the 4th edition of Dietary Guidelines for Chinese Elderly Residents (2016) by the Chinese Nutrition Society (29) that will be given to the participant separately. If a participant does not prepare his or her own meals, the person who does the cooking receives the dietary advice as well. A dietary checklist aiming to evaluate the compliance will be delivered with the pamphlet and patients will send it back after 1-week's recording.

### Measurements and Outcomes

#### Timing of Assessment

Study assessments will be performed at baseline, 4, 8, and 12 months unless otherwise stated below. For Group B, C and D, an additional assessment will be performed at 16-month follow-up.

#### Food and Nutrient Intake

The primary outcome measure will be changes in intake of fresh fruits and fresh vegetables measured at 4 months using the 24-h dietary recall method. Protein% of total energy will also be calculated. Three 24-h dietary recall will be conducted through face-to-face interview, twice on weekdays and once on weekend. The data on food consumption will be converted into the corresponding nutrient contents based on the 6th version of China Food Composition Tables Standard Edition. Moreover, a modified simplified food-frequency questionnaire (FFQ) of 33 food group items (30) will be conducted at baseline, 4, 8, 12, and 16 months.

#### Masticatory Function

Masticatory function will be assessed at baseline (before treatment) and 4, 8, 12 and 16 months after insertion of a fixed implant retained prosthesis using the quantitative method described by Schimmel et al. (31) as previously described (32). In brief, subjects will be asked to mix a two-color chewing gum with 20 masticatory cycles. The obtained bolus will be pressed to a standardized height and a color image will be acquired. Quantitative data will be obtained by digital analysis of the image using variance of hue as the outcome.

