#### Study Overview

The study is designed as a factorial randomized controlled clinical trial testing the benefits of dental and/or dietary interventions on changes in fresh fruits and fresh vegetables intake at 4 months (Table 1). Group A (DE+/DI+) will receive the full treatment regimen. Group B (DE+/DI–) will receive implant-supported fixed prosthesis at first and nutrition education after a 4-month waiting period. Group C (DE–/DI+) will receive the nutrition education at first and implant treatment after a 4-month waiting period. Group D (DE–/DI–) will receive the same treatment as Group A after a 4-month waiting period (Figure 1). The waiting period is equal to the current waiting list in the department. Subjects will be followed for an additional 12-month period. All procedures will follow the principles of the Declaration of Helsinki on experimentation involving human subjects, all subjects will provide written informed consent. The trial has been approved by the Institutional Review Board of the Shanghai Ninth People's Hospital, Shanghai Jiao Tong University School of Medicine (Approval No. SH9H-2021-T321-3) and is registered in ClinicalTrials.gov (NCT05334407). The trial will be independently monitored by the office of clinical research of the Shanghai Ninth People's Hospital. Any modifications to the protocol with impact on the conduct of the study will require a formal amendment to the protocol. The SPIRIT summary of the trial procedures is illustrated in Supplementary Table 1.

**Table 1 T1:** Overview of the schedule of enrolment, interventions, and assessments.

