**Assessments**								
*24-h dietary recall*	X			X				
*food-frequency questionnaire*	X			X	X	X	X	
*Anthropometric measurement*	X			X	X	X	X	
*Masticatory function*	X			X	X	X	X	
*Peri-implant soft tissue condition*				X	X	X	X	
*OHIP-14*	X			X	X	X	X	
*Blood sample*	X			X	X	X	X	
*Saliva sample*	X			X	X	X	X	
*Subgingival plaque sample*	X			X	X	X	X	
*Stool sample*	X			X				
*Nutritional status*	X			X	X	X	X	
*Muscle strength*	X			X	X	X	X	
*Cognitive function*	X			X	X	X	X	
*Depressive symptoms*	X			X	X	X	X	

* *Interventions included DE (dental intervention) and DI (Dietary Intervention)*.

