##### Inclusion Criteria

Being edentulous or having a terminal dentition (22) and accepted treatment plan for fixed implant-supported prosthesis restoring at least 10 pairs of occluding teeth.Self-reported inadequate fresh vegetables or fresh fruits or protein foods intakes (daily intake thresholds based on the Chinese Dietary Guidelines for the Elderly recommendations).Understanding written and spoken Chinese and ability to respond to Chinese questionnaires.Able and willing to give informed consent for participation in the study.Able and willing to comply with 12-month follow-up.

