#### Peri-Implant Soft and Hard Tissue Health

Peri-implant soft tissue condition will be measured by periodontal probing (UNC/CP-11.5B Screening Color-Coded Probe, Hu-Friedy, Chicago, IL, USA). Modified plaque index (mPI), probing depth (PD), and modified bleeding index (mBI) will be evaluated (33). Standardized panoramic radiographic imaging will be conducted to assess the peri-implant bone level. The assessment will be performed at 4-, 8-, and 12-month post-surgery.

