##### Oral and Fecal Microbiome

Oral rinse, subgingival plaque and fresh stool samples will be collected for 16S rRNA gene sequencing at baseline, 4, 8, 12, and 16 months.

Oral microbiome samples will be obtained by oral rinsing for 1 min with 5 mL of buffer solution (38, 39). Additionally, in dentate patients a subgingival plaque sample will be taken from the deepest periodontal pocket/lesion with a sterile paper point inserted to the depth of the pocket. The subgingival plaque sample will be collected after isolating the sampling area with cotton rolls gentle air drying, and supragingival plaque removal. Samples will be immediately stored at −80°C.

Sterile stool tube with a spatula inside will be given to the participants with detailed instructions on how to collect the specimen. Fresh stool samples will be collected by the participants at home the night before the visit day or the morning of the visit day (40). Samples will be stored in the patient's refrigerator at 4°C until submission. During transportation, samples will be kept on ice in a cooling bag.

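### Masticatory function has two clocks: if the post-insertion timing in the text is followed, Groups C and D have no month-4 value; stool visits and Group A's month-16 visit also disagree

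*Protocol article*

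**What the plan says.** All references are to the protocol article.

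- **Masticatory Function** sets a pre-treatment baseline and then tests at "4, 8, 12 and 16 months after insertion of a fixed implant retained prosthesis".
- **Table 1** has a row "Masticatory function" ticked at enrolment and at 4, 8, 12 and 16 months. Its time axis runs from allocation, each of these visits has a window of 14 days either side, and assessment rows are not split by group.
- **Timing of Assessment** gives the general rule: "Study assessments will be performed at baseline, 4, 8, and 12 months unless otherwise stated below". It then adds: "For Group B, C and D, an additional assessment will be performed at 16-month follow-up". Group A is not named.
- **Study Overview** says that Group B "will receive implant-supported fixed prosthesis at first and nutrition education after a 4-month waiting period". Group A gets the full regimen without a wait. Groups C and D get the prosthesis only after 4 months. All subjects are then followed for a further 12 months. The abstract gives follow-up as 16 months.
- **Dental Intervention** describes two prostheses: an interim one within 24 hours of surgery and a definitive one after 4 months of healing.
- **Oral and Fecal Microbiome** says "fresh stool samples will be collected for 16S rRNA gene sequencing at baseline, 4, 8, 12, and 16 months". Table 1 ticks stool at enrolment and month 4 only.
- **Inclusion Criteria** requires "Able and willing to comply with 12-month follow-up".

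**The concern.** The factorial comparison is made at 4 months from allocation. Masticatory function is a stated outcome, and restoring it is the purpose of the dental intervention. To compare the arms with immediate dental treatment (A, B) and delayed dental treatment (C, D) as randomised, the chewing test must be done at the same study time in all four.

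A clock that starts at insertion does not do that. The delayed arms have no prosthesis during the factorial phase, so on that clock they have no visit at month 4. A missed month-4 test cannot be recovered later, because C and D are then treated. If the dietary result turned out null, the trial could not show by randomised comparison whether chewing had improved at the time diet was measured.

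The stool conflict decides whether there are any gut microbiome data after month 4. The Group A conflict decides whether one arm of four is seen at month 16.

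**Working it through.** **Inputs.** Planned n = 120, allocated 1:1:1:1, so 30 per group. Dental treatment starts at study month 0 in A and B and at about month 4 in C and D (Study Overview). Baseline is taken as the enrolment visit, as in Table 1.

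**Follow-up length first.** 4-month factorial phase + 12 further months = 16 months, which reproduces the abstract's figure.

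**Masticatory visits.** Study month of visit = month of insertion + 4, 8, 12 or 16.

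| Reading | Groups A, B | Groups C, D |
|---|---|---|
| Table 1 | 4, 8, 12, 16 | 4, 8, 12, 16 |
| Text, insertion = interim prosthesis (month 0 or 4) | 4, 8, 12, 16 | 8, 12, 16, 20 |
| Text, insertion = definitive prosthesis (4 months later) | 8, 12, 16, 20 | 12, 16, 20, 24 |

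On the interim reading, C and D (2 × 30 = 60 of 120) have no month-4 value, and their last test falls 20 − 16 = 4 months after the trial closes. On the definitive reading, no group has a month-4 value. The 14-day window cannot absorb a 4-month gap. The section does not say which prosthesis it means.

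Under Table 1, every group is tested at month 4. Time since insertion at the four visits is then 4, 8, 12, 16 months in A and B and 0, 4, 8, 12 months in C and D.

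**Stool.** Table 1: 2 visits × 120 = 240 samples at most. Text: 5 visits × 120 = 600 if Group A attends month 16, or 4 × 120 + 90 = 570 if only B, C and D do. No reading satisfies both schedules.

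**Group A at month 16.** Timing of Assessment gives the visit to B, C and D (90 participants). The abstract, Study Overview and Table 1 make no exception for A (30 participants). Nor do the sections on the food-frequency questionnaire, plasma nutrient biomarkers, microbiome, nutritional status, muscle strength and cognition.

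**The case against.** The best defence is that the Masticatory Function section is loosely worded. Several other outcome sections give the same list of months in study time, and this one differs by a single added phrase. Table 1 is clear and excludes no group, so a sensible site would test everyone at month 4. That is a fair reading, and it makes the loss conditional. It does not remove the conflict, because the general timing rule expressly yields to later sections and this later section states a different clock.

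It is also fair that masticatory function is not the primary outcome. The 4-month timing of the 24-hour recall is consistent across the abstract, Study Overview, Table 1 and Food and Nutrient Intake.

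A reader might infer more than the documents support:

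- *That the waiting arms simply lack a month-4 value.* This follows only if the text overrides Table 1. It also does not describe Group B on the interim reading: B waits for diet advice, not for the prosthesis.
- *That the peri-implant schedule conflicts too.* That section says "The assessment will be performed at 4-, 8-, and 12-month post-surgery". With surgery at month 0 or about month 4, this gives study months 4, 8, 12 (A, B) and 8, 12, 16 (C, D). Together these are the columns ticked in Table 1, whose rows do not claim to apply to every group at every visit.
- *That eligibility secures too little follow-up.* The 12 months in the criterion can mean the 12-month extension described in Study Overview and the Discussion. The wording is ambiguous, not a demonstrated shortfall.
- *That dental treatment in C and D starts at month 8.* This rests on the intervention columns of Table 1, which may have been displaced in conversion from PDF. Nothing here relies on them.

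**Conclusion.** The point holds as an internal inconsistency. The text and Table 1 give incompatible schedules for masticatory function. If the text is followed with insertion taken as the interim prosthesis, 60 of 120 participants have no month-4 value for the randomised dental comparison, and their last test is due at about month 20 of a 16-month trial. If insertion means the definitive prosthesis, no group has a month-4 value. If Table 1 is followed, nothing is lost.

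The stool conflict (five visits against two) is unconditional. Group A's month-16 visit is a smaller ambiguity affecting 30 participants at one late visit.

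This rests on dental treatment starting at month 0 in A and B and about month 4 in C and D, as Study Overview states, and on equal groups of 30. It does not touch the timing of the primary outcome. It is worth correcting because a missed month-4 chewing test cannot be recovered.

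**What to change.** 1. In Masticatory Function, time the test from randomisation in every group: baseline and study months 4, 8, 12 and 16, as in Table 1. Record time since insertion as a secondary variable, and say whether it counts from the interim or the definitive prosthesis. State that the month-4 test in C and D is done before their prosthesis is placed.
2. Make Oral and Fecal Microbiome and Table 1 agree on the stool visits.
3. Make the abstract, Study Overview, Timing of Assessment and Table 1 agree on whether Group A has a 16-month visit.
4. State in the inclusion criterion that the commitment covers the whole follow-up (16 months from randomisation, if that is what is meant).

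The cost is amendment wording. Item 1 adds no visits beyond those in Table 1. Item 2 adds stool samples to Table 1 only if the five-visit schedule is the intended one: 330 to 360 more at most (570 − 240 or 600 − 240).

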#### Peri-Implant Soft and Hard Tissue Health

Peri-implant soft tissue condition will be measured by periodontal probing (UNC/CP-11.5B Screening Color-Coded Probe, Hu-Friedy, Chicago, IL, USA). Modified plaque index (mPI), probing depth (PD), and modified bleeding index (mBI) will be evaluated (33). Standardized panoramic radiographic imaging will be conducted to assess the peri-implant bone level. The assessment will be performed at 4-, 8-, and 12-month post-surgery.

#### Oral Health Impact Profile (OHIP)-14

The oral health impact profile (OHIP)-14 (34) will be administrated to assess the impact of oral health on the quality of life of participants using a validated Chinese translation of the instrument (35).

#### Biological Samples

Biological samples will be collected and processed in a standard way by dedicated study personnel blind with respect to treatment status. The blood sample collection will be scheduled at 8 a.m.-9 a.m. Patients will fast overnight (12–14 h) prior to blood collection. Subjects will be advised to avoid strenuous exercise 1 h prior to collection. Samples will be processed at the clinical research center laboratory to meet the preservation standards for the assay of each marker and will be either assayed immediately or stored at −80°C in the Shanghai Ninth People's Hospital Biobank facility for later analysis.

##### Metabolic and Inflammatory Biomarkers

The following biomarkers will be assessed by a specialized GCP approved clinical pathology laboratory.

a) Blood serum concentration of homocysteine.b) Plasma hs-CRP, TNF-α, IL-1βand IL-6.c) Co Q10, Uric acid and superoxide dismutase.d) Blood lipids (total cholesterol, HDL cholesterol, LDL cholesterol, triglycerides and Lpa).

##### Plasma Nutrient Biomarkers

Nutrient biomarkers will be assessed at baseline, 4, 8, 12, and 16-month follow-up by an accredited laboratory according to international standards.

a) Plasma vitamins A, B2, B12, folate, C and E will be measured by liquid chromatography-mass spectrometry (LS-MS).b) Plasma carotenoids (α- and β-carotene, β-cryptoxanthin, lycopene, lutein/zeaxanthin) and tocopherols (α- and γ) will be measured by LS-MS.

##### Plasma Metabolomics

a) Metabolites will be profiled with untargeted metabolomics using liquid chromatography coupled with mass spectrometry (36).b) Oxylipin changes will be assessed by oxidative lipidomics (37).

##### Oral and Fecal Microbiome

Oral rinse, subgingival plaque and fresh stool samples will be collected for 16S rRNA gene sequencing at baseline, 4, 8, 12, and 16 months.

Oral microbiome samples will be obtained by oral rinsing for 1 min with 5 mL of buffer solution (38, 39). Additionally, in dentate patients a subgingival plaque sample will be taken from the deepest periodontal pocket/lesion with a sterile paper point inserted to the depth of the pocket. The subgingival plaque sample will be collected after isolating the sampling area with cotton rolls gentle air drying, and supragingival plaque removal. Samples will be immediately stored at −80°C.

Sterile stool tube with a spatula inside will be given to the participants with detailed instructions on how to collect the specimen. Fresh stool samples will be collected by the participants at home the night before the visit day or the morning of the visit day (40). Samples will be stored in the patient's refrigerator at 4°C until submission. During transportation, samples will be kept on ice in a cooling bag.

#### Nutritional Status

Mini-nutrient status form (MNA-SF) (41) will be used to screen patients for risk of malnutrition at baseline, 4, 8, 12, and 16 months.

#### Muscle Strength

A hand grip dynamometer will be used to assess muscle strength at baseline, 4, 8, 12 and 16 months essentially as described (32).

#### Cognitive Function

Cognitive function will be assessed with the Mini-Mental State Examination (MMSE) (42) and the Ascertain Dementia 8 (AD8) questionnaire (43) at baseline, 4, 8, 12, and 16 months.

#### Depression Symptoms

Depressive symptoms will be assessed with the shortened Center for Epidemiologic Studies Depression Scale (CES-D10) (44).

### Safety Evaluation

#### Adverse Events

The collective evidence from numerous clinical trials reveals consistent findings that the implant supported fixed full-arch prosthesis is a safe and effective treatment approach for terminal dentition or full edentulism. Dietary advice is also a safe intervention for edentulous elderly. No significant adverse events have been reported. Occasionally the patient may experience early implant failure and/or mechanical complications of the prosthesis. These will be recorded in the case report forms and will be managed according to standard of care with additional implant placement or refabrication/modification of the existing prosthesis.

#### Follow-Up for Adverse Events

Adverse events (AE), if any, will be managed according to current standard of care for the specific condition and will be reported to the ethics committee. The principal investigators will assess and manage the condition to the best of his knowledge and refer to specialist care if appropriate and in the best interest of the participant. AE will be considered resolved once the principal investigators concur that to be the case.

